
### Data management and analysis

After completion of data collection, raw data will be entered in prepared electronic databases and merged with the electronically captured data. The accuracy of data will be checked by two independent researchers. Data saving and storage will be performed in accordance with the German regulation of Good Clinical Practice [95].

In addition to the quantitative data, feasibility will be analysed using qualitative data, such as answers to open questions in the satisfaction questionnaires and verbal information.

Descriptive statistics will be used to summarize the sample characteristics (e.g. sex, age, and symptom duration) and two-tailed independent *t-*tests will be used to test for significant differences between the intervention and control groups at enrolment (t2).

Subjects will be analysed on an intention-to-treat basis. To examine the course of the symptoms, related variables will be analysed using the pre–post point estimate comparisons, variability estimates, and 95% confidence intervals. The controlled study design allows for within-group as well as between-group comparisons. Paired-sample *t*-tests will be used for within-group comparisons, while the independent *t-*test will be used for between-group comparisons.

The significance level for all *t-*tests will be set at *p* < 0.05.

The analyses of the course of the symptom-related variables will function as estimates of the effect sizes, while effect estimates can be obtained for physiotherapy and psychotherapy separately as well as the overall effect estimates. These estimates can be used to determine the optimal sample size for a subsequent RCT with a normally distributed sample; hence, parametric tests will be applied as statistical procedures in the feasibility study. Factors influencing therapy success will also be examined.

Statistical analyses will be performed with IBM SPSS Statistics, Version 24 (IBM, Armonk, NY, USA).

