### Procedure

In a first step, all eligible patients who were examined in the interdisciplinary CPPS outpatient clinic since 2012 (time point t1), and are thus part of the observational cohort, will be identified and assigned to either the treatment group or the control group. Detailed information about the pilot study will be sent to these patients by postal mail, whereby the informed consent signed previously by patients for the assessment at the outpatient clinic facilitates contacting them for future research. Patients willing to participate in either the treatment group or the control group will undergo a telephone interview to re-examine eligibility in case changes have occurred since their visit to the outpatient clinic and to answer open questions about the study. After inclusion, participants will receive two copies of the informed consent document, the final time schedule and a set of questionnaires (time point t2; see Instruments for a detailed description). Participants of the treatment group will also be contacted by a physiotherapist to schedule an examination appointment. Patients who do not meet inclusion criteria will be informed by telephone and will receive support regarding alternative treatment options, if requested. Patients’ reasons for non-participation, if given, will be documented. In addition, patients who do not respond to the initial letter will also be contacted by telephone.

Further measurements will be conducted at the beginning (t3) and end of the first intervention module (t4) and at the beginning (t5) and the end of the second intervention module (t6) as well as 4 weeks after finishing the second intervention module (t7). The study procedure is in line with the Standard Protocol Items: Recommendations for Interventional Trials (SPIRIT) statement 2013 [46] (see also Additional file 1: SPIRIT checklist). Figure 2 displays the schedule of enrolment, interventions, and assessments according to the SPIRIT statement.

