The group assignment will be based on the ability of regular participation in the intervention which might lead to selection bias. However, we deemed regular attendance important for the positive effect of the whole intervention programme, and as the complete intervention will last 22 weeks (each intervention module has a duration of 9 weeks with a 4-week break in between) it will require a great concession in terms of time. Participants will not only have a weekly appointment at University Medical Center Hamburg-Eppendorf, they will also have to prepare the psychotherapeutic sessions by reading the workbook chapters and completing the respective questionnaires. It is unclear whether patients will comply with these requirements so that they will be prepared enough to follow and understand the content of the single psychotherapeutic sessions. Moreover, it is expected that at least some subjects will miss one or more sessions due to shift work, unplanned vacations, or other reasons. This might result in difficulties in understanding the content of the subsequent sessions, influencing the effect of the intervention. However, the subjects will have manuals for both the psychotherapy and physiotherapy components, which will allow them to educate themselves even if they have missed a session. Both intervention modules will be applied in a subsequent order rather than to deliver physiotherapy and psychotherapy at the same time. This approach was chosen so that participants have to make time for a weekly appointment and estimate the effects of each module separately. Nonetheless, some patients might find it tempting to select the intervention module they find more interesting or suitable for their individual situation and skip the other one. In addition, the subsequent order contributes to the prolongation of the overall treatment period. All psychotherapy sessions will be provided as group treatments. Group sessions will be accompanied by a workbook, which requires that participants adhere to specific assignments and may influence their motivation. Nonetheless, the workbook provides support and advice both during the intervention period and after its completion.

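### The t2-to-t7 effect estimates are labelled intention-to-treat, but the t-tests named for them, with no imputation stated, give available-case estimates

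*Protocol article*

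**What the plan says.** All of this is in the protocol article.

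- **Principle.** Data management and analysis: "Subjects will be analysed on an intention-to-treat basis".
- **Tests.** The same section: "Paired-sample *t*-tests will be used for within-group comparisons, while the independent" t-test serves the between-group comparisons. Changes are to be reported as pre-post "point estimate comparisons, variability estimates, and 95% confidence intervals". The reason given for parametric tests is normality in the later trial; missing values are not mentioned.
- **Use.** The same section, the Objectives and the Sample section intend the effect estimates for sizing a later randomised trial. Estimates are wanted for each module separately and overall.
- **Schedule.** Procedure: after t2, "Further measurements will be conducted at the beginning (t3) and end of the first intervention module (t4"), then at t5 and t6 for the second module and at t7, four weeks after it ends. Under Control group, controls are measured at t2 and t7 only.
- **Expected loss.** The Intervention group section chooses a group size meant to withstand drop-outs. Instruments counts drop-outs as an acceptability indicator. The Discussion describes a demanding 22-week programme and adds: "Nonetheless, some patients might find it tempting to select the intervention module they find more interesting".

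**The concern.** The label promises that every assigned patient counts in the assigned group. The named tests deliver this only if every patient has the values that the test needs, or if missing values are filled in by some stated method. The article states no such method. An intervention patient measured at t2 to t5 and then lost would contribute nothing to the t2-to-t7 comparison, although four of the six measurements were collected.

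Patients lost from a long and demanding programme may well have a different course from those who stay. If so, the overall effect size handed to the planners of the later trial describes the patients who could still be measured, while the label tells them that it describes everyone assigned. That trial could be planned too small.

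**Working it through.** **Which data each test uses when nothing is imputed**

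| Comparison | Values needed | Who is left out |
|---|---|---|
| Intervention vs control at t2 | t2 | only patients without t2 |
| Paired t2 to t7 | t2 and t7 | anyone without t7, whatever was measured at t3 to t6 |
| Intervention vs control at t7, or on change | t7 (and t2 for change) | anyone without t7 |
| Paired module comparison (t3 to t4, or t5 to t6) | both ends of the module | anyone missing either end |

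The label and the tests therefore part company in the second and third rows, which are the overall estimates. In the fourth row, the second-module estimate rests on patients still measured in that module, so the module and overall estimates can rest on different patients.

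**Size of the possible bias.** The article gives no drop-out rate, effect size or SD, and says that no sample size calculation was done, so there is no figure of its own to reproduce. Everything below is assumption apart from the group sizes 36 and 18 (Sample section).

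Let *d* be the fraction lost, with a change of 0.5 SD in observed patients and *c* in lost patients:

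all-patient mean = (1 − *d*) × 0.5 + *d* × *c*

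The last two columns carry the mean into a later 1:1 trial, taking it as the between-group difference δ in SD units, with 80% power and two-sided 0.05:

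n per arm = 2 × (1.960 + 0.8416)² / δ² = 15.70 / δ², rounded up. For δ = 0.5: 15.70 / 0.25 = 62.8, so 63.

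| *d* | Mean, *c* = 0 | Overstatement (0.5 / mean − 1) | Mean, *c* = 0.25 | n per arm, *c* = 0 | n per arm, *c* = 0.25 |
|---|---|---|---|---|---|
| 10% | 0.450 | 11% | 0.475 | 78 | 70 |
| 15% | 0.425 | 18% | 0.4625 | 87 | 74 |
| 20% | 0.400 | 25% | 0.450 | 99 | 78 |
| 30% | 0.350 | 43% | 0.425 | 129 | 87 |
| 35% | 0.325 | 54% | 0.4125 | 149 | 93 |

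If *c* = 0.5, the mean is 0.5 at every *d*, there is no bias, and 63 per arm stands.

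**Precision.** Half-width of the 95% interval for the between-group difference, in SD units = t(0.975, n₁ + n₂ − 2) × √(1/n₁ + 1/n₂).

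- Full sample, 36 vs 18: 2.007 × √(1/36 + 1/18) = 2.007 × 0.289 = 0.58.
- 20% lost in each group (36 × 0.8 = 28.8, so 29; 18 × 0.8 = 14.4, so 14): 2.020 × √(1/29 + 1/14) = 2.020 × 0.325 = 0.66.

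**The case against.** The strongest reply is that the article is silent rather than contradictory. It never says that patients without follow-up are deleted, t-tests can be run on imputed data, and a missing-data rule is commonly left to a full protocol or analysis plan that is not shown. This stands as far as it goes: the absence of a rule is not the error, and label and tests are not incompatible in logic. But the article itself chooses the two-point tests and justifies them by normality alone. For an intervention group measured six times, in a study that expects drop-out, that choice can be judged as it is written.

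A reader might infer more than the documents support, in three ways.

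- *That this is a completer analysis.* It is not. The article does not say that patients who stop sessions are no longer measured. Someone who skips a module but returns the t7 questionnaires stays in the t2-to-t7 comparison in the assigned group, as intention-to-treat requires.
- *That t3 to t6 data go unused.* They can enter the separate module comparisons. A patient who leaves after the first module with t3 and t4 measured counts in that module's estimate. The loss concerns the t2-to-t7 estimates.
- *That every t-test is affected.* The enrolment tests, described as "tests will be used to test for significant differences between the intervention and control groups at enrolment (t2"), need no second value.

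Two further points stand. The outcomes are secondary: the primary outcome is feasibility, the Sample section disclaims proof of efficacy, and drop-out will itself be reported. A mixed model is also no cure for loss that depends on unobserved outcomes.

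**Conclusion.** The point holds in a limited form. As written, the overall estimates would be available-case estimates carrying an intention-to-treat label, and they would ignore intermediate data already collected on intervention patients lost before t7.

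The size cannot be known from the article. With an observed change of 0.5 SD, the overstatement is 18-54% at 15-35% loss if lost patients do not change at all, smaller if they change somewhat, and zero if they change like the others. For the later trial, the number needed ranges from the planned 63 per arm to about double at 30% loss (129 / 63 = 2.05). The loss rates, the 0.5 SD and the course of lost patients are all assumptions, so the 54% figure should not be read as an expected bias.

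The feasibility conclusions are untouched. The change is still worth making, because sizing the later trial is a stated purpose of these estimates.

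**What to change.** For each repeatedly measured score, make the main analysis one linear mixed model (MIXED in SPSS, the software already named) on all available t2 to t7 data of every assigned patient.

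- **Fixed effects:** visit, treatment sequence and sex, with the intervention-control contrast estimated only at t2 and t7, because controls have no t3 to t6 data.
- **Covariance:** a parsimonious structure, for example compound-symmetric. An unstructured matrix over six visits has 6 × 7 / 2 = 21 parameters, with at most 36 patients informing t3 to t6.
- **Results:** read the t2-to-t7 and module contrasts from this model with 95% intervals.
- **Supplementary:** keep the t-tests, labelled available-case, and report the number of patients in each.

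If the t-tests must remain the main analysis, either state how patients without follow-up values enter them or replace the intention-to-treat label.

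The cost is a change of analysis wording and modest programming, with the same data and software. Trial status reports the study as ongoing with further groups planned, so the change can still be made. The limits are that the model relies on missing-at-random, which is weaker than the assumption behind case deletion but still an assumption, and that it cannot recover change for controls without t7.

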### Sample

Study subjects will be recruited from the observational cohort consisting of all patients assessed at the interdisciplinary outpatient clinic for CPPS at the University Medical Center Hamburg-Eppendorf.

The following criteria will be applied to identify eligible patients in the observational cohort: CPPS diagnosis according to the EAU guidelines [1] and classification of the International Association for the Study of Pain [44], informed consent, sufficient German language skills, age > 18 years, and score ≤ 40 for the mental or physical scale of the 12-Item Short-Form Health Survey (SF-12) [45]. Exclusion criteria are delusional disorders, substance dependence (except nicotine or pain medication), acute suicidal tendencies, planned absences over the treatment period, and current psychotherapy or physiotherapy.

The targeted sample size for the study is 54 participants. Thirty-six participants will be assigned to the intervention group and 18 to the control group. This sample size allows for evaluation of the study in terms of feasibility and can be used to estimate therapeutic effects (pre–post and between groups). Although the sample size is not sufficient to prove the efficacy of the combined treatment programme, the results of the study can be used to calculate the sample size for a subsequent RCT.

Assignment of eligible subjects to treatment and control groups will not be randomized; instead, it will be determined by the ability to regularly participate in the treatment sessions at the University Medical Center Hamburg-Eppendorf. Regular participation is defined as a maximum miss of four of the 18 treatment sessions. The assignment to one of the two treatment sequences (starting with psychotherapy vs starting with physiotherapy) will be randomized.

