### Intervention group

The intervention will consist of two consecutive treatment modules (cognitive behavioural group psychotherapy and physiotherapy as both group and individual sessions). A 4-week break is scheduled between the two modules. The intervention group has two branches; therefore, subjects will start with either one of the modules described in the following. A group size of nine patients for the psychotherapy as well as for the physiotherapy group sessions is regarded as adequate even in the event of drop-outs. This group size also reflects the maximal number of patients allowed in a CBT group in the German healthcare system [47]. The groups will be gender homogeneous because CPPS is characterized by symptoms in an intimate body region potentially associated with shame [48]. With a targeted sample size of 36 participants in the intervention and a group size of nine in the therapeutic sessions, the overall intervention group will consist of four therapeutic groups, two with only male participants and two with only female participants. One group of each gender will start with either psychotherapy or physiotherapy, resulting in four treatment groups in the intervention group.

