7	Group discussion/debriefing of Chapter 6 of the patient workbook; exercise of PMR; theory: coping strategies (Part 1)/role of positive self-messages; behaviour analysis	Group (90 min)
8	Group discussion/debriefing of Chapter 7 of the patient workbook; exercise of PMR; theory: coping strategies (Part 2); activity and inactivity/recognizing avoidance behaviour; behaviour analysis	Group (90 min)
9	Group discussion/debriefing of Chapter 8 of the patient workbook; exercise of PMR; assessment of changes during the programme; revision of key topics	Group (90 min)

*min* minutes, *PMR* progressive muscle relaxation

The patient workbook for cognitive behavioural group psychotherapy has been designed by members of our study group, and is based on the work of Tripp, Nickel, and Mullins [50, 51] who developed a treatment rationale for individual therapy and demonstrated its feasibility and yielded first indicators of its efficacy [35]. Through cooperation with the Canadian workgroup, we were able to translate, expand, and adapt their patient workbook [51] to the needs of our study and the German healthcare system. Key topics for the cognitive behavioural intervention are as follows:coping with catastrophizing cognitions,reduction of avoidance behaviour/increase of physical activity,development of coping strategies, andenhancing social support.

Furthermore, behaviour analysis also plays a key role in the programme. As group therapy facilitates the acquisition of new behaviour patterns [52], behaviour changes are addressed in the group setting. To increase the possibility of implementation into the German healthcare system we adapted the workbook to a group context.

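### Post-treatment t-tests involving the intervention arm treat patients from shared therapy groups of about nine as independent, so secondary confidence intervals are too narrow if outcomes correlate within groups

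*Protocol article*

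**What the plan says.** In the Protocol article, Data management and analysis names the outcome tests: "Paired-sample *t*-tests will be used for within-group comparisons, while the independent *t-*test will be used for between-group comparisons". It sets one threshold, "The significance level for all *t-*tests will be set at *p* < 0.05", and asks for pre–post estimates with 95% confidence intervals.

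The numbers come from Sample: "Thirty-six participants will be assigned to the intervention group and 18 to the control group". Intervention group describes delivery: "A group size of nine patients for the psychotherapy as well as for the physiotherapy group sessions is regarded as adequate", and "the overall intervention group will consist of four therapeutic groups, two with only male participants and two with only female participants". All nine psychotherapy sessions are group sessions; in Physiotherapy, units 1, 5 and 9 are group sessions and the other six are individual. The section on cognitive behavioural psychotherapy gives the group a therapeutic role: "behaviour changes are addressed in the group setting". Under Control group, controls receive no study treatment and use their own local care.

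The analysis section has no term for therapy group or therapist, and the article mentions no ICC, mixed model or robust standard error. Trial status lists two groups treated in 2016, two in the first half of 2017 and two more planned for July 2017, which makes six.

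**The concern.** Patients who attend the same sessions with the same therapists and the same fellow patients can come to resemble one another in outcome. Here 12 of 18 sessions (9 psychotherapy + 3 physiotherapy) are shared, and the protocol counts on the group to help change behaviour. Positive correlation within groups is therefore plausible in the treated arm, while controls have no such structure. This is a partially nested design.

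A t-test on 36 treated patients counts 36 independent pieces of information. If outcomes correlate within groups there are fewer, and the standard error, confidence interval and p-value all overstate precision. Two analyses are exposed: paired tests of change in the intervention arm once group treatment has begun, and the intervention-versus-control comparison after treatment. Preliminary efficacy is the declared secondary objective, and the article says the estimates can be used to size a later randomised trial. Readers will therefore use these intervals to judge how well the effects are known.

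The article itself fixes these tests, so this is not a detail left to a separate analysis plan.

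**Working it through.** The plan has no power or sample-size calculation to reproduce. Its counts agree: 36/9 = 4 groups and 36 + 18 = 54 patients.

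**Inputs from the article.** Treated n = 36 and controls n = 18 (Sample); group size m = 9, four groups (Intervention group); level 0.05 (Data management and analysis).

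**Assumptions.** ICC of the analysed outcome (change score or t7 score) 0.02 to 0.10, since none is given; equal variances in both arms; two-sided outcome tests, since the article states two-tailed testing only for the enrolment comparison.

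**Formulas.**
- Design effect in the intervention arm: DE = 1 + (m − 1) × ICC
- Effective treated n = 36/DE
- True/calculated SE, paired test: √DE
- True/calculated SE, treated versus control: √[(DE/36 + 1/18)/(1/36 + 1/18)] = √[(DE + 2)/3]

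For ICC 0.05: DE = 1 + 8 × 0.05 = 1.40; effective n = 36/1.40 = 25.7; paired ratio √1.40 = 1.18; between-group ratio √(3.40/3) = 1.06 to 1.07 (1.065).

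Type I error was simulated with 100,000 trials per scenario under the null: treated patients with group variance ICC and residual variance 1 − ICC, 18 independent controls, ordinary t-tests.

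Four groups of nine:

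| ICC | DE | Effective n | SE ratio, paired | SE ratio, between | Type I, paired | Type I, between |
|---|---|---|---|---|---|---|
| 0 | 1.00 | 36.0 | 1.00 | 1.00 | 5.0% | 5.1% |
| 0.02 | 1.16 | 31.0 | 1.08 | 1.03 | 6.8% | 5.5% |
| 0.05 | 1.40 | 25.7 | 1.18 | 1.065 | 9.5% | 6.4% |
| 0.10 | 1.80 | 20.0 | 1.34 | 1.13 | 14.5% | 8.3% |

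A test that allows unequal variances gives nearly the same between-group values (5.6%, 6.4%, 8.1%).

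Six groups of six, assuming the treated total stays at 36:

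| ICC | DE | SE ratio, paired | SE ratio, between | Type I, paired | Type I, between |
|---|---|---|---|---|---|
| 0.02 | 1.10 | 1.05 | 1.02 | 6.2% | 5.4% |
| 0.05 | 1.25 | 1.12 | 1.04 | 7.9% | 6.0% |
| 0.10 | 1.50 | 1.225 | 1.08 | 11.0% | 7.1% |

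**Effect on the intervals (four groups of nine).** In SD units of the analysed variable, the unadjusted 95% half-width is 2.03/√36 = 0.338 within the arm and 2.007 × √(1/36 + 1/18) = 0.579 between arms. Multiplying by the SE ratios gives 0.36, 0.40 and 0.45 within the arm, and 0.59, 0.62 and 0.65 between arms, for ICC 0.02, 0.05 and 0.10.

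**The case against.** The strongest reply is that nothing decisive rests on these tests. The primary outcome is feasibility (demand, acceptability, practicality), and the article says plainly that the sample cannot prove efficacy and that the study is exploratory. This stands, and it lowers the severity. It does not answer the point, because a small sample does not justify an interval narrower than the data support.

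The size is also uncertain. Six of nine physiotherapy units are individual, the article does not say membership is closed, and Trial status points to more and perhaps smaller groups. All of this stands. In the comparison with controls, the 18 ungrouped controls supply two thirds of the unadjusted variance, so the inflation there is modest.

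Three stronger readings are tempting, and the documents do not support them.
- *Every t-test is affected.* The t2 comparison precedes group treatment, so it has no treatment-induced clustering. The paired test in the control arm involves no therapy groups.
- *The comparison of the two treatment sequences is worst hit.* No such t-test is specified. The between-group comparison described is intervention against control.
- *A trial sized from these results would be too small because of these tests.* Sample size depends on the effect estimate and the SD. With equal groups, clustering does not bias the mean change, and it lowers the expected treated-arm variance only to (36 − DE)/35 = 0.995 to 0.977 of its value, about 1% on the SD at most. The article does not say that the later trial would omit a design effect.

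Finally, a mixed model is not an easy cure. Four groups, one for each gender and sequence combination, leave group variance confounded with both factors. An analysis of the four group means has 3 degrees of freedom (critical value 3.18, against 2.03 with 35). This stands and shapes the remedy.

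**Conclusion.** The point holds in limited form and is a should-fix. For any positive ICC, the stated paired tests of post-treatment change in the intervention arm and the stated post-treatment tests against controls give standard errors that are too small. The paired pre–post intervals carry most of the problem; the controlled comparison is affected modestly at small ICCs. If the ICC is zero there is no error.

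The direction follows from the design and the named tests. The size rests on the assumed ICC range, on four groups of nine and on equal arm variances, and it shrinks but does not vanish with six groups of six. The documents cannot settle the ICC, so the result should be read as a range.

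**What to change.** In Data management and analysis, add the following.

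1. Report 95% confidence intervals for post-treatment change in the intervention arm and for intervention versus control both unadjusted and with the intervention-arm variance multiplied by 1 + (m − 1) × ICC, for ICC 0.02, 0.05 and 0.10, where m is the group size actually reached. For the difference between arms, use SE = √(DE × s²_T/n_T + s²_C/n_C), so that the control term stays as it is.
2. Describe the p-values from these tests as descriptive.
3. Fit a partially nested mixed model (random effect for therapy group in the intervention arm only, separate residual variances by arm, small-sample degrees of freedom) as a sensitivity analysis only, and say that the group variance is barely estimable.
4. State that a later trial sized from these estimates needs a design effect for therapy groups. As an illustration, in a 1:1 trial of groups of nine against ungrouped controls with equal variances, the required n rises by the factor (DE + 1)/2, which is 8%, 20% or 40% at ICC 0.02, 0.05 or 0.10.

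No new data are needed if each patient's therapy group is recorded. The cost is a little extra analysis and moderately wider intervals: 8% to 34% within the intervention arm and 3% to 13% between arms with four groups of nine. Intervals based on the mixed model could be much wider, which is a further reason to keep it as a sensitivity analysis.

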## Methods/design

### Study design

This study will be conducted based on the principles of a ‘cohort multiple randomized controlled trial’ (cmRCT) proposed by Relton et al. [43]. In this pragmatic study design, an observational cohort of subjects with the parameter of interest will be recruited and evaluated on a regular basis. For a randomized controlled trial, random subjects from all eligible subjects in the cohort are allocated to the intervention group, while allocation to the control group is not randomized [43].

The feasibility study is embedded in the Interdisciplinary Research Platform Chronic Pelvic Pain Syndrome (CPPS), which was initiated in 2012 at the University Medical Center Hamburg-Eppendorf to obtain insight into the somatic and psychological aspects in CPPS and to develop treatment strategies for these patients. In cooperation with different medical specialties (e.g. psychosomatic medicine, urology, gynaecology, and physiotherapy), a specialized outpatient clinic for patients with CPPS was implemented [5]. The assessment at this outpatient clinic includes a diagnosis of CPPS according to the EAU guidelines [1]. People diagnosed with CPPS constitute the observational cohort, from which subjects for this study will be recruited.

The treatment will consist of a combination of cognitive behavioural psychotherapy and physiotherapy based on an aetiological model developed especially for patients with CPPS [6]. Psychotherapeutic and physiotherapeutic treatment modalities will be applied as consecutive modules, and both sequences will be tested (psychotherapy followed by physiotherapy vs physiotherapy followed by psychotherapy). The intervention will therefore consist of two branches, one starting with psychotherapy and the other starting with physiotherapy. For a detailed overview of the study design, see Fig. 1.

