### Control group

Allocation to the control group will not be randomized; instead, this will be determined by the ability to participate in the intervention occurring at the University Medical Center Hamburg-Eppendorf. It was considered difficult for patients outside the greater Hamburg area to participate; therefore, they will be allocated to the control group. The control group will not receive any specific intervention as part of the study; nonetheless, patients can seek treatment as usual from their local healthcare provider. Assessment of the control group will be done at two time points; first, at time point t2, which is the enrolment time; and second, at time point t7, which is 4 weeks after the intervention group has finished the second intervention module. The results of these measurements will be compared with the results of the intervention group to gather initial insight into the efficacy of the intervention compared to treatment as usual.

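### The non-randomised comparison with control is analysed only by an unadjusted t-test whose outcome (t7 score or change) is not stated; moderate weight, secondary aim only

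*Protocol article*

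**What the plan says.** **Allocation.** The Sample section says: "Assignment of eligible subjects to treatment and control groups will not be randomized; instead, it will be determined by the ability to regularly participate". The Control group section gives the working rule: "It was considered difficult for patients outside the greater Hamburg area to participate; therefore, they will be allocated to the control group". Only the order of the two modules is randomised. The Study design section describes the cohort multiple RCT model as one in which "random subjects from all eligible subjects in the cohort are allocated to the intervention group".

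**Analysis.** In Data management and analysis, paired t-tests serve the within-group comparisons and an independent t-"test will be used for between-group comparisons". No covariate is named, and all t-tests use a 0.05 level. Two-tailed t-tests are also planned to "test for significant differences between the intervention and control groups at enrolment (t2"), with no stated consequence for the effect analysis. The section speaks of pre–post estimates with confidence intervals, but does not say whether the between-group test takes the t7 score or the change from t2.

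**Use.** The Control group section wants a first look at efficacy against usual care from this contrast. Data management and analysis intends the effect estimates to help size a later RCT. The Discussion concedes possible selection bias and offers no analytic remedy.

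**The concern.** A plain t-test suits groups made comparable by design, and these are not. Patients who came to a specialised clinic from outside the region may differ from local patients in severity or duration. That is plausible, but the protocol does not document it. Sex may differ too: the intervention arm is fixed at two male and two female groups of nine, while no sex composition is given for the 18 controls, and the NIH-CPSI has a modified version for women.

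The t2 tests do not protect the comparison. They are weak at this size, and the plan does the same thing whichever way they fall. Leaving the outcome open matters as well, because the two possible t-tests respond to the same baseline gap with different, sometimes opposite, bias. An estimate wrong by a quarter to half an SD would be a poor basis for sizing the next trial.

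**Working it through.** **The plan's own figure.** Four groups × 9 = 36 in the intervention group; 36 + 18 = 54. This is consistent. The protocol gives no power, effect size or SD, and says that no sample size calculation was done, so there is nothing further to reproduce.

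**Inputs.** From the protocol: n = 36 and 18, alpha 0.05, controls measured at t2 and t7. Assumed: a two-sided effect test (two-tailed is stated only for the t2 tests), a t2 gap d = 0.5 SD, a t2–t7 correlation r of 0.5 to 0.7, equal SD at both times, and no true treatment effect.

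**1. What the t2 test can see.** The standard error of a mean difference in SD units is √(1/36 + 1/18) = 0.289. The noncentral t with 52 df gives these powers:

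| t2 imbalance (SD) | Power |
|---|---|
| 0.3 | 17.5% |
| 0.5 | 39.8% |
| 0.8 | 77.6% |

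Power reaches 80% at 0.82 SD. A 0.5 SD imbalance would therefore be missed about 60% of the time.

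**2. Bias from a 0.5 SD gap.** There are two limiting cases. In the first the gap regresses: t7 depends on t2 alone, in the same way in both groups. In the second it is stable: the groups differ by d at both times.

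- t-test on t7: r × d if regressing, d if stable.
- t-test on change: −(1 − r) × d if regressing, 0 if stable.
- Linear model of t7 on group and t2 (ANCOVA): 0 if regressing, (1 − r) × d if stable.

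False-positive rates come from a simulation with 20,000 replicates per scenario.

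| Analysis | Regressing: bias (SD) | False positives | Stable: bias (SD) | False positives |
|---|---|---|---|---|
| t7 score | 0.25 to 0.35 | 14–22% | 0.50 | 40% |
| Change | −0.25 to −0.15 | 10–13% | 0.00 | 5% |
| ANCOVA on t2 | 0.00 | 5% | 0.25 to 0.15 | 16–11% |

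Ranges run from r = 0.5 to r = 0.7.

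**3. Precision.** The variance of the group difference is proportional to 1 for t7 scores, 2(1 − r) for changes and 1 − r² for ANCOVA.

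- ANCOVA against t7: 1/(1 − r²) = 1.33 at r = 0.5 and 1.96 at r = 0.7, a gain in effective sample size of 33–96%.
- ANCOVA against change: 2/(1 + r) = 1.33 at r = 0.5 and 1.18 at r = 0.7, a gain of 33% falling to 18%.
- 95% CI half-width: 0.58 SD on t7 scores. On changes it is 0.58 × √(2(1 − r)), or 0.58 to 0.45 SD. With ANCOVA it is 0.58 × √(1 − r²), or 0.50 to 0.41 SD.

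These gains are for balanced baselines and are slightly smaller when t2 is imbalanced.

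**The case against.** The strongest reply concerns weight. The primary aim is feasibility, and none of its indicators depends on this test. The protocol says that the sample cannot prove efficacy, presents the contrast as initial insight, and openly concedes selection bias. This stands, and keeps the point at moderate severity.

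A reader might infer that any t2 difference passes straight into the efficacy estimate. The document does not support that as a fact. It would be so only if t7 scores were compared and the gap were stable, and the reference to the course of symptoms and to pre–post estimates is at least as compatible with change scores. The 96% upper precision gain likewise applies only against a t7 t-test. The 0.5 SD gap is hypothetical: no t2 data are shown, and both groups come from one clinic under the same eligibility criteria.

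Nor is ANCOVA uniformly better here. With a stable gap it leaves (1 − r) of the difference, while change scores leave none. This too stands, and is why the fix includes both.

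A reader might also think that the cohort-multiple-RCT label conceals the lack of randomisation. It does not: the Sample and Control group sections both state it. What remains is a matter of wording.

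Finally, a sex quota for controls might seem to follow. It does not. An article's silence on the controls' sex mix is not a stated error. A quota would change recruitment in an ongoing study that draws on a cohort of limited size, and adjustment for sex suffices.

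**Conclusion.** The concern holds at moderate severity, for the secondary efficacy comparison only. The protocol fixes an unadjusted test for groups that are not randomised, leaves open which outcome it compares, and relies on t2 tests that are weak and without consequence.

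Under an assumed 0.5 SD gap and an assumed correlation of 0.5–0.7, the bias ranges from 0.25 SD against the direction of the gap (changes, regressing) to 0.50 SD along it (t7 scores, stable). The power figure of about 40% needs no correlation assumption, only the planned group sizes and the 0.05 level. Whether an imbalance of this size will occur cannot be judged from the document. Adjustment for t2 reduces the exposure but does not guarantee its removal, and unmeasured differences tied to residence would remain.

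**What to change.** - Make the between-group estimate a prespecified linear model of the t7 score on group, the t2 value of the same score, sex and symptom duration. Report it with a 95% CI and fit it whatever the t2 tests show.
- Report the change-score comparison as a sensitivity analysis and say why: the two methods are unbiased under different assumptions about the gap, so disagreement between them is informative.
- Show standardised differences at t2.
- Describe the comparison with control as non-randomised, state that only module sequence is randomised, and note possible residual confounding by residence.

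Cost: changes to the analysis section and to wording, with no new data, since both groups are assessed at t2 and t7 and sex and symptom duration are already recorded. With complete data the model has 54 − 5 = 49 residual degrees of freedom against 52 for the t-test.
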